### Secondary endpoints

Accuracy, specificity, and sensitivity are evaluated using the following gold standards: postoperative histopathology of ultrasonic gastroscopy for tumor invasion depth, abdominal and pelvic enhanced computed tomography (CT) scan for LNM, pathological biopsy for tumor differentiation, and auxiliary examination for TNM staging.Cut-off values for LNM: A receiver operating characteristic curve is drawn for the clinical characteristics under different LNM rates to obtain the cut-off values.Logistic regression model: To explore the corresponding logistic regression model, postoperative histopathological examination for LNM, depth of infiltration, and degree of differentiation are evaluated in the univariate analysis. Variables with statistical significance in the univariate analysis are examined in the multivariate analysis.Complications: The incidence of postoperative complications within the last 30 days, including anastomotic fistula, pancreatic fistula, intestinal obstruction, delayed bleeding, and incision-related complications, are recorded. Postoperative complications classified as higher than Grade II, according to the Clavien–Dindo classification are regarded as clinically significant (Tables 2), [16].Five-year relapse-free survival rate: The time interval from the date of operation to the detection of tumor recurrence within 5 years is recorded.

**Table 2 Tab2:** Clavien–Dindo classification

Grade	Definition
I	Any complication that deviates from the natural course of the operation; treatments include antiemetic, antipyretic, analgesic, and diuretic drugs; infusion; physical therapy; as well as bedside debridement of incision infection.
II	Medications other than those permitted for grade I complications are required, including blood transfusion and total parenteral nutrition support.
III	Surgical and endoscopic interventions and radiotherapy are required.
IIIa	No general anesthesia is required.
IIIb	General anesthesia is needed.
IV	Life-threatening complications requiring intensive care.
IVa	Single-organ dysfunction
IVb	Multi-organ dysfunction
V	Death

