## Methods/design

### Study aim

This study aims to explore and evaluate expanded indications for ESD that match the characteristics of the Chinese population in patients with EGC, and to introduce a staging procedure and examination scheme for EGC that is appropriate for China.

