### Study design and setting

This is a multicenter, ambispective, observational, open-cohort study. The clinical trial was launched in May 2018 and will end in March 2022, with enrollment to be completed by December 2021. Between May 2018 and December 2022, patients from Beijing Friendship Hospital, Capital Medical University, Beijing Cancer Hospital, Peking University People’s Hospital, Peking University First Hospital, Chinese PLA General Hospital, and Cancer Hospital Chinese Academy of Medical Sciences will be selected for treatment. In total, 554 patients are expected to be included in the trial. After providing written informed consent, patients will undergo a D2 gastrectomy in a non-randomized, prospective study. For the retrospective study, researchers will recruit patients from January 2008 to April 2018, and all enrolled patients must meet the inclusion criteria. The detailed research process is described in Fig. 1. The latest protocol version is version 1.0 in April 2018.

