### Inclusion criteria

Patients aged 18–75 years (regardless of sex).Patients with Eastern Cooperative Oncology Group (ECOG) score ≤ 2 points and American Society of Anesthesiologists (ASA) score ≤ 2 points who can undergo a radical D2 gastrectomy.Patients without a history of gastrointestinal operation, chemotherapy, or radiotherapy.Patients with normal liver, kidney, heart, lung, and bone marrow function (GPT × 10^9^/L, PLT>10^9^/L).Patients who can understand and comply with the research protocol.Patients who can provide written informed consent by themselves or through their legal agent.Gastroscopic and pathologic diagnoses based on the following criteria: ①Tumor diameter > 30 mm, ulceration (UL)(+), and differentiated, mucosal carcinoma (T1a); ②Tumor diameter > 30 mm and differentiated, submucosal invasion depth < 500 μm (T1b SM1); ③Tumor diameter ≤ 30 mm and differentiated, submucosal carcinoma (T1b); ④Tumor diameter ≤ 20 mm, UL(−), and undifferentiated (T1a); ⑤Tumor diameter > 20 mm, UL(−), and undifferentiated (T1a); ⑥Tumor diameter ≤ 30 mm, UL(+), and undifferentiated (T1a); ⑦Tumor diameter > 30 mm, UL(+), and undifferentiated (T1a). The detailed inclusion criteria are shown in Table 1.

**Table 1 Tab1:** Inclusion criteria of expanded indications for ESD in patients with EGC

	T1a				T1b			
	UL (−)		UL (+)		SM1		SM2	
	≤20 mm	> 20 mm	≤30 mm	> 30 mm	≤30 mm	> 30 mm	≤30 mm	> 30 mm
**Differentiated**	ESD	ESD	ESD	EXPANDED	EXPANDED	EXPANDED	EXPANDED	SURGERY
**Undifferentiated**	EXPANDED	EXPANDED	EXPANDED	EXPANDED	SURGERY	SURGERY	SURGERY	SURGERY

ESD, ESD absolute indication; EXPANDED, ESD expanded indication; SURGERY, surgical indication for EGC; EGC, early gastric cancer; ESD, endoscopic submucosal dissection

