### Informed consent

According to the requirements of the ethics committee, all enrolled patients must sign an informed consent document. Informed consent forms are provided to the patients before their enrollment in the prospective study; the consent forms include information on the purpose and significance of the study, the benefits and possible risks of participating in the study, and the confidentiality of the study. Enrolled patients have the opportunity to ask questions and receive answers. The requirement for informed consent is waived due to the retrospective nature of study.

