### Statistical analysis

SPSS 21.0 (IBM Corp., Armonk, NY, USA) statistical software is used for the statistical analysis. The quantitative variables are described as the mean ± standard deviation and are tested by univariate analysis of variance for normal distribution; on the contrary, they are described as the median (interquartile range) and tested by the Kruskal-Wallis H test for non-normal distribution. The categorical variables are described as frequency (N) with the percentage (%) and tested by χ^2^ test, corrective χ^2^ test, or Fisher’s exact test. Ranked data are expressed as frequency and percentages and are compared using the Kruskal-Wallis H test. Sensitivity and specificity are calculated to evaluate the diagnostic performance. The Kaplan-Meier method is used to draw survival curves, and the survival of multiple groups are compared by the log-rank test. The univariate and multivariate Cox proportional hazards models are used to evaluate the hazard ratios for adverse outcomes. All statistical tests are two-sided, and a *P*-value < 0.05 is considered statistically significant.

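### Prospective patients are admitted on the depth and biopsy readings whose sensitivity and specificity are then estimated, so those two measures cannot be carried over to EGC in general

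*Protocol article*

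**What the plan says.** One of the two study aims is "to introduce a staging procedure and examination scheme for EGC that is appropriate for China" (Study aim). Secondary endpoints serves it with accuracy, specificity and sensitivity judged against "postoperative histopathology of ultrasonic gastroscopy for tumor invasion depth, abdominal and pelvic enhanced computed tomography (CT) scan for LNM, pathological biopsy for tumor differentiation", together with TNM staging. Statistical analysis adds only that "Sensitivity and specificity are calculated to evaluate the diagnostic performance".

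Entry is by "Gastroscopic and pathologic diagnoses based on the following criteria" (Inclusion criteria). Seven combinations of depth, differentiation, ulceration and size follow, summarised in Table 1. Undifferentiated tumours are admitted only as T1a (criteria 4 to 7). T1b tumours are admitted only if differentiated (criteria 2 and 3). Differentiated T1a tumours are admitted only if ulcerated and over 30 mm (criterion 1).

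On timing, Informed consent states: "Informed consent forms are provided to the patients before their enrollment in the prospective study". Table 3 places consent before the operation, and Study design and setting has D2 gastrectomy follow it. Elimination criteria then provides for removing patients found at pathology to have advanced or non-gastric cancer. For the other part of the cohort, Study design and setting says: "For the retrospective study, researchers will recruit patients from January 2008 to April 2018, and all enrolled patients must meet the inclusion criteria". Determination of sample size splits the 554 patients into 274 prospective and 280 retrospective.

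**The concern.** Prospective patients are enrolled before the specimen exists, so depth and differentiation at entry must be preoperative readings. The same kinds of reading are then assessed for sensitivity and specificity. Both measures need patients with positive and negative readings to be sampled fairly within each true state, and the entry rule does not do that. It admits or refuses a patient according to the reading, and by a different rule for each histology.

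A staging scheme needs to know how well depth and biopsy assessment perform in patients with EGC who have not yet been classified. If the estimates partly reflect the mix of admitted categories, they could make an examination look better or worse than it is. The analysis stage cannot repair this, because patients with refused readings are not in the data.

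**Working it through.** **Plan's own figure.** The article gives no sample size or precision for the accuracy endpoints. Its one calculation, for the LNM rate, reproduces: 1.96² × 0.03 × 0.97 / 0.015² = 496.8, rounded up to 497. The point does not depend on it.

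**Step 1: which depth readings can enter (criteria 1 to 7, Table 1).**

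| Biopsy | Ulcer | ≤20 mm | >20 to 30 mm | >30 mm |
|---|---|---|---|---|
| Differentiated | UL(−) | SM1, SM2 | SM1, SM2 | SM1 |
| Differentiated | UL(+) | SM1, SM2 | SM1, SM2 | T1a, SM1 |
| Undifferentiated | UL(−) | T1a | T1a | T1a |
| Undifferentiated | UL(+) | T1a | T1a | T1a |

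In 11 of 12 strata only T1a or only T1b readings are admitted. If the entry reading is the test under evaluation, sensitivity/specificity for submucosal invasion there is 0%/100% or 100%/0% by construction. Biopsy type mirrors this. Every T1b reading carries a differentiated biopsy, so sensitivity for undifferentiated type is 0% among them. Both biopsy types occur together only for T1a, UL(+), over 30 mm. None of this needs a numerical assumption.

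**Step 2: pooled values.** Let a be the chance of entry given a T1a reading and b the chance given a T1b reading, with entry depending on true depth only through the reading. Then

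- apparent sensitivity = Se·b / [Se·b + (1 − Se)·a]
- apparent specificity = Sp·a / [Sp·a + (1 − Sp)·b]

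These equal the true values only if a = b.

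*Set A (assumed).* Se 72%, Sp 85%; 40% truly submucosal in each histology; 10% of differentiated T1a readings and 80% of differentiated T1b readings eligible; undifferentiated T1a readings all eligible, undifferentiated T1b readings none. The Discussion cites 72% as ultrasound accuracy in T1b staging; its use as sensitivity is an assumption.

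Differentiated patients, per patient in the source population:
- sensitivity = (0.40 × 0.72 × 0.80) / (0.40 × 0.72 × 0.80 + 0.40 × 0.28 × 0.10) = 0.2304 / 0.2416 = 95%
- specificity = (0.60 × 0.85 × 0.10) / (0.60 × 0.85 × 0.10 + 0.60 × 0.15 × 0.80) = 0.051 / 0.123 = 41%

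Pooled, with source share u undifferentiated: a = 0.10(1 − u) + u and b = 0.80(1 − u).

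| u | a | b | Undifferentiated share of cohort | Apparent Se / Sp |
|---|---|---|---|---|
| 20% | 0.28 | 0.64 | 30% | 85% / 71% |
| 33% | 0.40 | 0.53 | 46% | 77% / 81% |
| 50% | 0.55 | 0.40 | 63% | 65% / 89% |
| 67% | 0.70 | 0.27 | 77% | 49% / 94% |

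The test is the same in every row.

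*Set B (assumed, with the criteria applied cell by cell).* Se 72%, Sp 80%; biopsy 90% sensitive and specific; 30% ulcerated; 35% over 30 mm; 40% of T1b readings SM1. With a differentiated biopsy, a = 0.30 × 0.35 = 0.105 and b = 0.40 + 0.60 × 0.65 = 0.79. With an undifferentiated biopsy, a = 1 and b = 0. The share with an undifferentiated biopsy is r = 0.90u + 0.10(1 − u), so pooled a = 0.105(1 − r) + r and b = 0.79(1 − r).

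- u = 20%: r = 0.26, a = 0.338, b = 0.585, giving 82% / 70%
- u = 35%: r = 0.38, a = 0.445, b = 0.490, giving 74% / 78%
- u = 65%: r = 0.62, a = 0.660, b = 0.300, giving 54% / 90%

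Over 1,152 assumed case mixes the error was −22 to +16 points for depth sensitivity, −29 to +12 for depth specificity, 0 to +9 for biopsy sensitivity and −19 to 0 for biopsy specificity.

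**Step 3: do pooled values still follow the test?** Yes. In Set B at u = 35%, true values of 60/70, 72/80 and 90/90 appear as 62/68, 74/78 and 91/89. Here a and b happen to be close.

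**Step 4: selection on pathology instead.** If the 280 retrospective patients were chosen on the specimen, entry would not depend on the reading. Then a = b within each true state, and under Set A the formulas return 72%/85%. What is lost is spectrum: with no undifferentiated pT1b tumours, sensitivity in undifferentiated disease cannot be estimated.

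**Step 5: T category.** Every admitted patient is read as T1. If tumours of pT2 or deeper are eliminated, every analysed patient is also pT1, and agreement on T1 versus deeper is 100% by construction. The elimination wording joins advanced stage to distant metastasis with an "and", so how many such patients would go is unclear.

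**The case against.** The strongest reply is that the 0%/100% results arise within histology strata, while the article plans no accuracy analysis by stratum. Pooled estimates follow the test, sometimes to within about 2 points (Step 3), and the large distortions come from the ends of assumed ranges. This stands in part. A reader might infer that eligibility largely fixes the planned figures, and the documents do not support that. They do support a bias of unknown size and direction, since the article gives no case mix from which to judge it.

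Second, the entry reading need not be ultrasound. Inclusion criteria asks only for a gastroscopic diagnosis, Data collection allows ultrasound or magnified gastroscopy, and Quality control of gastroscopy treats ultrasound as conditional. Where another assessment set the entry category, the ultrasound depth is not forced. This stands and limits the depth result. It does not help biopsy differentiation if the entry biopsy is the one evaluated.

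Third, a reader might extend the argument to all 554 patients. The article does not say whether retrospective eligibility rests on preoperative readings or on pathology, and pathology-based selection would restrict the spectrum without fixing the reading (Step 4).

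Fourth, a reader might conclude that the staging aim as a whole fails. It does not: CT nodal status is not an entry criterion, and the Abstract already lists consistency between preoperative examinations and pathology among the endpoints.

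Leaving the matter to a statistical analysis plan would not answer it, because the entry rule and the endpoint are both fixed in this article.

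**Conclusion.** The point holds for depth, differentiation and T category in the 274 prospective patients, to the extent that the reading used for entry is the one evaluated. Within most strata, sensitivity and specificity for depth are then set by the entry rule. Pooled, they are biased by an amount that depends on how often each kind of reading is admitted. In the assumed scenarios the depth error ranges from near zero to more than 20 points, in either direction. Those sizes rest on case-mix and accuracy inputs that the article does not supply; the one-sided strata rest only on Table 1. The estimates therefore describe the admitted categories and cannot be carried over to EGC patients in general. The design can still estimate what pathology shows once a patient has been classified as expanded indication. This concerns a secondary endpoint that serves a stated aim; it should be changed, and it does not touch the primary LNM rate.

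**What to change.** In Secondary endpoints and Statistical analysis:

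- For depth, differentiation and T category, make the accuracy measure the proportion of each admitted preoperative category that is confirmed, up-staged or down-staged at pathology, with confidence intervals.
- Keep patients found to be pT2 or deeper in this denominator, even if they are eliminated from the LNM analysis. Otherwise up-staging beyond T1 cannot be counted and confirmation is overstated.
- State that the results apply to patients already classified as expanded indication.
- Report the prospective and retrospective parts separately, and state whether retrospective eligibility rests on preoperative readings or on pathology.
- Keep sensitivity and specificity for CT and LNM.

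For the prospective part this uses data already being collected. The price is a narrower accuracy claim and modest precision per category. If the 274 patients spread evenly over the seven categories, each has about 274 / 7 = 39, and the 95% half-width at 50% is 1.96 × √(0.25 / 39) = 0.157, about 16 points. If sensitivity and specificity for EGC at large are still wanted, they need a separate set of EGC resections not filtered by preoperative category, at the cost of extra chart abstraction.

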**Methods:**

This is a multicenter, ambispective, observational, open-cohort study that is expected to enroll 554 patients with EGC. The study was launched in May 2018 and is scheduled to end in March 2022. All enrolled patients should meet the inclusion criteria. Case report forms and electronic data capture systems are used to obtain clinical data, which includes demographic information, results of perioperative blood- and auxiliary examinations, surgical information, results of postoperative pathology, and the outcomes of postoperative recovery and follow-up. Patients are followed up every 6 months after surgery for a minimum of 5 years. The primary endpoint is the rate of lymph node metastasis (LNM), whereas the secondary endpoints include the following: consistency, sensitivity, and specificity of the results of preoperative examinations and postoperative pathology; cut-off values for LNM; logistic regression model of expanded indications for ESD; and incidence of postoperative complications within the 30-day and 5-year relapse-free survival rates.

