#### Data collection

A uniform case report form (CRF) was designed, and the electronic data capture (EDC) system was already established before the commencement of the clinical trial. All data are provided on the CRF. Subsequently, the clinical research coordinator (CRC) enters the data into the EDC system promptly (https://edc-cloud.medsci.cn/#/login). Every month, clinical research associates monitor the electronic database to ensure data quality.

The CRF includes the following data: 1) Demographic information: sex, age, length of hospital stay, body mass index, family disease history, concomitant disease, ECOG score, nutrition risk screening 2002 (NRS 2002) score, and venous thromboembolism score; 2) Perioperative laboratory tests: results of routine blood tests, biochemical investigations, and tumor marker evaluations, including CA19–9, CA125, AFP, CEA, and CA724; 3) Auxiliary examination: all the enrolled patients undergo an abdominal enhanced CT scan and low-dose plain CT scan of the chest, a positron emission tomography (PET)/CT examination when necessary, and an ultrasound gastroscopy or magnified gastroscopy; 4) Surgical information: ASA score, operation date, operation time, blood loss, surgical methods, degree of lymph node dissection, and intraoperative complications; 5) Postoperative pathology: the number of tumor lesions, tumor size, tumor location, surgical margin, gross type of tumor, histopathological type, Lauren type, depth of tumor invasion, number of lymph nodes dissected, and total number of LNM; and 6) Postoperative recovery outcomes: total hospitalization cost, postoperative complications and death, and recovery time of intestinal function (Table 3).

**Table 3 Tab3:** Checklist for the collection of necessary clinical data and follow-up scheme of enrolled patients with EGC

	Baseline information		Follow-up after operation													
	Preoperation	Operation	POD 1	POD 3	POD 7	POD 30	6 months	1 year	18 months	2 years	30 months	3 years	42 months	4 years	54 months	5 years
**Informed consent**	×															
**Demographic information**	×															
**Laboratory tests**	×		×	×	×	×	×	×	×	×	×	×	×	×	×	×
**Chest CT scan**	×							×		×		×		×		×
**Abdominal CT scan**	×						×	×	×	×	×	×	×	×	×	×
**Gastroscopy**	×							×		×		×		×		×
**Abdominal ultrasound**	×						×	×	×	×	×	×	×	×	×	×
**Physical examination**	×						×	×	×	×	×	×	×	×	×	×
**Surgical information**		×														
**Pathology**		×														

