### Determination of sample size

The sample size was calculated by PASS 11.0 (NCSS Statistical and Data Analysis, USA) software and was estimated based on the preliminary research results of the Japanese clinical trial. According to previous studies with a single group design, the rate of LNM with expanded indications for ESD was 3% [20, 21] with an allowable error of 1.5%. Based on a one-sided test with an α value equal to 0.025, the estimated total sample size required for the trial is at least 497 patients. The withdrawal rate was assumed to be 20% during the follow-up. Therefore, the total sample size that is needed for this clinical study is approximately 554 patients, of which 274 and 280 are enrolled in a prospective- and retrospective study, respectively.

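### As worded, the exploratory LNM logistic model names only depth and differentiation as predictors, leaving tumour size and ulceration, the other two factors that define the expanded indications, with no stated route in

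*Protocol article*

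**What the plan says.** The abstract lists among the secondary endpoints a "logistic regression model of expanded indications for ESD". The Secondary endpoints section describes how it is built: "postoperative histopathological examination for LNM, depth of infiltration, and degree of differentiation are evaluated in the univariate analysis". The next sentence gives the entry rule: "Variables with statistical significance in the univariate analysis are examined in the multivariate analysis".

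The Inclusion criteria and Table 1 define the expanded indications by four factors: depth, differentiation, tumour diameter and ulceration (UL). The undifferentiated T1a categories are separated by diameter and ulceration alone. The first two, for example, read "④Tumor diameter ≤ 20 mm, UL(−), and undifferentiated (T1a); ⑤Tumor diameter > 20 mm, UL(−), and undifferentiated (T1a".

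Under Data collection, the pathology items include "the number of tumor lesions, tumor size, tumor location, surgical margin, gross type of tumor", so size is captured. Ulceration is not named there, nor in the pathology or gastroscopy report templates under Quality control. The Statistical analysis section does not mention logistic regression.

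**The concern.** A model of the expanded indications should be able to use the factors that define them. Here the stated candidates are two of the four, and a variable can reach the multivariate step only through the univariate one. If that wording is followed, the model cannot give different LNM risks to indications that differ only in size or ulceration.

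There is a second consequence. Eligibility ties size and ulceration to depth among differentiated tumours. Leaving them out therefore mixes their effects into the depth coefficient, and the significance screen is then applied to that distorted coefficient.

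**Working it through.** **Plan's own figure.** The model has no sample size of its own, so the starting point is the precision calculation in Determination of sample size: LNM rate 3%, allowable error 1.5%, one-sided α 0.025.

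n = z² p(1−p)/d² = 1.96² × 0.03 × 0.97 / 0.015² = 496.8, rounded up to 497. The stated 497 is reproduced.

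**Covariate patterns.** Depth is coded T1a/SM1/SM2 and differentiation as two levels, as in Table 1.

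| Cell marked expanded | Size | UL | Pattern seen by the model |
|---|---|---|---|
| Differentiated T1a | > 30 mm | + | A |
| Differentiated SM1 | ≤ 30 mm | not split | B |
| Differentiated SM1 | > 30 mm | not split | B |
| Differentiated SM2 | ≤ 30 mm | not split | C |
| Undifferentiated T1a | ≤ 20 mm | − | D |
| Undifferentiated T1a | > 20 mm | − | D |
| Undifferentiated T1a | ≤ 30 mm | + | D |
| Undifferentiated T1a | > 30 mm | + | D |

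Eight cells give four patterns. A model with an intercept, one differentiation term and two depth terms has four parameters, so by maximum likelihood it fits each pattern's average risk exactly. Pattern D receives one risk for four categories, and pattern B one risk for two.

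**Illustration for pattern D (assumptions, not document figures).** Equal cell sizes, 1% risk in the lowest cell, and the same odds ratio (OR) for the larger size class and for ulceration. The lowest-cell odds are 0.01/0.99 = 0.0101, and cell odds are 0.0101 × OR^k, where k = 0, 1, 1, 2.

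- OR 1: all cells 1.0%, model 1.0%, no error.
- OR 2: 1.0%, 2.0%, 2.0%, 3.9%. Model: (1.00 + 1.98 + 1.98 + 3.88)/4 = 2.2%.
- OR 3: 1.0%, 2.9%, 2.9%, 8.3%. Model: (1.00 + 2.94 + 2.94 + 8.33)/4 = 3.8%.

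Under OR 2 to 3 the lowest cell is overstated about 2- to 4-fold (2.2/1.0; 3.8/1.0). The highest is understated about 2-fold (3.9/2.2 = 1.8; 8.3/3.8 = 2.2).

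**Confounding of depth.** Differentiated T1a is eligible only if > 30 mm and UL(+), and differentiated SM2 only if ≤ 30 mm. Assume a true OR of 3 each for SM2 against T1a, for larger size and for ulceration. Relative to a small, non-ulcerated T1a tumour, the enrolled T1a group has odds 3 × 3 = 9. SM2 has odds 3 if UL(−), or 3 × 3 = 9 if UL(+). The apparent OR for SM2 against T1a is then 3/9 = 0.33 or 9/9 = 1.0, in place of 3. Under these assumptions depth would look protective or null.

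**Room for more terms.** Expected events at 3% are 497 × 0.03 = 14.9 and 554 × 0.03 = 16.6.

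- Three slopes (differentiation, SM1, SM2): 14.9/3 = 5.0 to 16.6/3 = 5.5 events per slope.
- Five slopes (adding size and UL): 14.9/5 = 3.0 to 16.6/5 = 3.3.

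The five-slope design over the eight cells has full rank (6 of 6 with the intercept), so it is estimable but thinly supported.

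**The case against.** The strongest case against is that the sentence is ambiguous. Grammatically LNM stands in the same list as depth and differentiation. The three could be examples, or simply the pathology results under study; the same three are targets in the diagnostic-accuracy endpoint. Nothing says the list is complete. This is also a condensed article, and a fuller covariate list may exist elsewhere. A reader might infer that size and ulceration are barred from the model, but the text does not support that. What stands is that the article gives a specific list and entry rule, and on no reading are size or ulceration named.

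A reader might also infer that the study as a whole cannot tell the expanded indications apart. That is not supported either. The Primary endpoint section gives the judging of indications to the LNM rate, and rates by category can be tabulated whatever the model contains. Such rates will be imprecise, at about two expected events per cell (15/8 to 17/8), but they exist.

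The ROC endpoint could yield a size cut-off: "A receiver operating characteristic curve is drawn for the clinical characteristics under different LNM rates to obtain the cut-off values". It names no characteristic, however, and is a separate endpoint not described as feeding the model. Finer coding of depth or histology could spread predicted risks within T1a, but not by size or ulceration.

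Finally, the base risk and odds ratios above are assumed. They show what could happen and do not measure this trial.

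**Conclusion.** The point holds in a limited form. As worded, the exploratory LNM model has two named predictors, and two of the four factors that define the expanded indications have no stated way in. If the list is followed literally with Table 1 coding, eight cells become four predicted risks, and the depth effect among differentiated tumours is confounded by eligibility. The cell count and the eligibility link follow from the document. The numerical size does not: it depends on the unknown effects of size and ulceration and is nil if both are null. The primary endpoint is unaffected. This should be corrected, but it is a defect of one secondary model and not of the study's main result.

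**What to change.** In the logistic-model item under Secondary endpoints:

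- State that LNM is the outcome.
- Prespecify depth, differentiation, tumour size (preferably continuous) and ulceration as predictors, entered together without univariate significance screening.
- Fit with a penalised likelihood, for example Firth. Firth's penalty pulls fitted risks towards one half, which at a rate near 3% means upwards, so re-estimate the intercept to make the mean predicted risk equal the observed rate.
- Report predicted LNM risk with confidence intervals for the expanded cells of Table 1. State the size and, for the T1b cells that the table does not split by ulceration, the ulceration status to which each prediction refers.
- Confirm that ulceration is recorded as a data item. It is needed to classify T1a tumours, but the T1b criteria do not mention it, so it could be missing for those patients.

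The cost is wording, modest analysis work and possibly one added data item. The real downside is precision. With about 15 to 17 expected events, roughly 3 per slope, intervals will be wide, so the model should be presented as exploratory, beside the tabulated category rates.

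### The univariate significance screen for the LNM logistic model can drop or reverse true risk factors, because eligibility ties depth inversely to differentiation

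*Protocol article*

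**What the plan says.** The Secondary endpoints section of the protocol article names depth of infiltration and degree of differentiation, taken from postoperative histopathology, for univariate analysis against LNM. It then sets the rule for what enters the model: "Variables with statistical significance in the univariate analysis are examined in the multivariate analysis". The Statistical analysis section makes all tests two-sided at P < 0.05 and gives no looser level for screening. Nothing in the article keeps either factor in the model regardless of its P value.

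The Inclusion criteria and Table 1 list seven eligible categories. One is differentiated T1a (ulcerated, over 30 mm). Two are T1b and both are differentiated, for example the category worded "and differentiated, submucosal carcinoma (T1b"). Four are undifferentiated and all are T1a. Table 1 assigns every undifferentiated T1b cell to surgery.

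Determination of sample size assumes that "the rate of LNM with expanded indications for ESD was 3% [20, 21] with an allowable error of 1.5"%, and concludes that "the estimated total sample size required for the trial is at least 497 patients".

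**The concern.** A univariate screen judges each factor without the other, which is safe only if the factors are roughly unrelated in the sample. Here eligibility relates them strongly. The T1a comparison group for T1b is mostly undifferentiated, and the differentiated comparison group for undifferentiated tumours is mostly T1b, unless differentiated T1a is common. Each factor is therefore compared with a group that carries the other risk. If both are harmful, the crude effects offset each other. If one is stronger, the weaker can look protective.

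The logistic model of expanded indications is a named secondary endpoint, and refining those indications is the study's aim. A model that omits depth or differentiation after a failed screen invites the reading that the factor does not matter for LNM.

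**Working it through.** **1. The plan's own figure and the event count.** Inputs from Determination of sample size: rate 3%, allowable error 1.5%, one-sided α 0.025 (z = 1.96).
n = 1.96² × 0.03 × 0.97 / 0.015² = 496.8, so 497, as stated.
Expected LNM events = 0.03 × 497 = 14.9 (95% binomial range 8 to 23). At 554 patients it is 16.6; at 554 × 0.8 = 443 it is 13.3.

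**2. Crude odds ratios by hand.** The article gives no odds ratios or case mix, so these are assumptions: the seven categories equally common (differentiated T1a : differentiated T1b : undifferentiated T1a = 1:2:4), overall LNM 3.2%, and a true odds ratio of 3.5 for each factor.
- Cell risks are 1.04%, 3.56% and 3.56%. Check: (1.04 + 2 × 3.56 + 4 × 3.56)/7 = 3.2.
- Depth: T1b 3.56% against T1a (1.04 + 4 × 3.56)/5 = 3.06%. Crude odds ratio 1.17.
- Undifferentiated 3.56% against differentiated (1.04 + 2 × 3.56)/3 = 2.72%. Crude odds ratio 1.32.

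With 5 for depth and 2 for undifferentiated type, the cell risks are 1.21%, 5.79% and 2.40%. Undifferentiated 2.40% is compared with differentiated (1.21 + 2 × 5.79)/3 = 4.26%, a crude odds ratio of 0.55 although the true value is 2.

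**3. How often the screen keeps each factor.** Simulation of 497 patients, LNM 3.2%, Fisher's exact test at two-sided 0.05, 4,000 trials per row. Restaging means that the stated share of patients changes depth/grade on final pathology.

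| True OR depth/undiff. | Case mix | Restaging | Crude OR depth/undiff. | Depth kept | Diff. kept | Neither kept |
|---|---|---|---|---|---|---|
| 3.5/3.5 | 1:2:4 | none | 1.17/1.32 | 6% | 5% | 90% |
| 3.5/3.5 | 1:3:3 | none | 1.22/1.22 | 6% | 5% | 90% |
| 3.5/3.5 | 1:1:1 | none | 1.57/1.57 | 13% | 12% | 75% |
| 3.5/3.5 | 1:2:4 | 10%/5% | 1.83/1.81 | 19% | 15% | 67% |
| 3.5/3.5 | 1:2:4 | 20%/10% | 2.37/2.30 | 35% | 27% | 45% |
| 5/2 | 1:2:4 | none | 2.78/0.55 | 48% | 18% | 51% |
| 5/2 | 1:1:1 | none | 3.34/0.68 | 60% | 7% | 39% |
| 5/2 | 1:2:4 | 10%/5% | 3.45/0.86 | 62% | 5% | 37% |
| 5/2 | 1:2:4 | 20%/10% | 3.98/1.19 | 71% | 5% | 27% |

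Other runs at the same restaging rates gave 64–66% for 10%/5% and 46% for 20%/10%. In the 5/2 row at 1:2:4 without restaging, nearly all of the 18% of trials that keep differentiation show undifferentiated type as protective. Where differentiated T1a is only 10% of patients, that crude odds ratio can be as low as 0.45.

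**4. Masking or too few events?** Both. An unmasked factor split 50:50, with about 15 events and an odds ratio of 3, is significant in only about 48–53% of trials. But the masking does not go away with numbers. With 5,000 patients (150 events), shares 20/40/40 and an odds ratio of 3 for each factor, the screen keeps each factor in 34% of trials, whereas a model holding both finds each in 98%.

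**The case against.** The strongest objection is restaging. Patients enter on gastroscopic and pathologic diagnosis, but the model uses postoperative histopathology. The Discussion cites endoscopic ultrasound accuracy of 78% overall and 72% for T1b submucosal staging. The elimination criteria remove pT2 disease, but not tumours that move to another T1 cell. Undifferentiated pT1b tumours will therefore enter the data and loosen the link. This stands, and it lowers the figures substantially, as the table shows. How far it applies to the 280 retrospective patients is unclear, because the article does not say whether they are classified from final pathology.

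Second, equal odds ratios give close to the fullest cancellation. With 5 and 2, depth often passes. This stands too, although differentiation is then still distorted or lost.

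Third, the model is exploratory and secondary. That limits the consequence but does not make the stated rule sound.

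A reader might also infer that the model's AUC and the ROC cut-offs will be badly over-optimistic. The documents do not allow that to be sized: they name only two candidate predictors, and internal validation and calibration are commonly left to an analysis plan that is not shown. Nor do they support treating the model as the sole route to refined indications, since the Primary endpoint section rests these on the presence and rate of LNM.

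**Conclusion.** The point holds as a fault in a stated analysis rule. Eligibility confounds the crude effects of depth and differentiation, and the plan selects variables on exactly those crude effects with about 15 expected events. If both factors raise risk, the screen can drop one or both, or show a harmful one as protective.

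A reader might infer that it will drop both. The documents do not support that: odds ratios, case mix and restaging are all assumed. At 3.5 each, neither is kept in about 75–90% of trials without restaging, and in about 65% or 45% under the two assumed restaging levels. At 5 and 2 without restaging, depth passes in about half or more of trials and the crude odds ratio for undifferentiated type is 0.55–0.68 at the tabulated mixes. The reversal fades with restaging and is gone at 20%/10%, but differentiation then passes in only 5%.

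The primary endpoint is unaffected. The rule should be changed, but it does not threaten the study.

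**What to change.** Delete the univariate screen. Prespecify the Table 1 factors (depth, differentiation, tumour size, ulceration), enter them together regardless of P value, and fit by Firth penalised logistic regression. Report adjusted odds ratios with confidence intervals, labelled exploratory. Univariate results can still be tabulated as description.

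The cost is analysis wording, and possibly R or an SPSS extension, since the plan names SPSS 21.0.

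The change removes the masking bias but not the shortage of events. With 20% differentiated T1a and no restaging, a model holding both factors detects each in about 28% of trials at a true odds ratio of 3 (screen: 8%) and 44% at 5 (screen: 9%). With only 10% differentiated T1a the gain is small, 9–15% against 6–7%. With all four factors in a Firth model at 3.5 each, neither depth nor differentiation is significant in 87%, 89% and 62% of trials at 1:2:4, 1:3:3 and 1:1:1. Intervals will stay wide, so the plan should also state that a non-significant term is not evidence of no effect.
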